## Methods

### Overview of Study Design

As described in Table 1, the study will draw on the preliminary validation data set and three original data sources.

**Table 1 table1:** Overview of approach.

Method	Sample	Aims	Analysis
Cognitive interviews (n=50)	25 (50% per language) sampled for maximum diversity	1: Cognitive evaluation and InDI^a^ revisions 2: Participant perspectives on attributions	1: Within- and between-interview analysis using Q-Notes 2: Qualitative analysis using grounded theory techniques
Previously collected validation data set (n=2583)	1518 (58.77%) in the United States 1065 (41.23%) in Canada	2: Intersectional psychometric evaluation	2: Exploratory factor analysis, exploratory structural equation modeling, and CFA^b^
Quantitative surveys	500 in Spanish^c^ 3000 in English^c^	2: Intersectional psychometric evaluation 3: Determine analytic utility of attributions	2: Multiple indicator multiple cause models and multigroup CFA 3: Descriptive statistics and multivariable regression models

^a^InDI: Intersectional Discrimination Index.

^b^CFA: confirmatory factor analysis.

^c^Quota sampling by race and ethnicity and sexual or gender minority status.

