### Participants

Eligible participants will be aged ≥18 years and residing in the United States. For cognitive interviews (25/50, 50% English; 25/50, 50% Spanish), participants will be of any race and ethnicity and purposively sampled to achieve maximum diversity in gender, sexual orientation, race and ethnicity, socioeconomic status, age, and nativity. Quota sampling will be used for the quantitative surveys. The Spanish survey (n=500) will include 250 SGM and 250 non-SGM. The English survey (n=3000) will include non-Hispanic Black (1000/3000, 33%), non-Hispanic White (1000/3000, 33%), and Hispanic or Latino/a/x persons of any race (1000/3000, 33%), with 50% (250/500 for Spanish and 1500/3000 for English) of each group being composed of SGM. We will further stratify recruitment by gender to generate sample sizes of approximately 250 at each race and ethnicity *SGM* gender intersection (eg, White non-SGM women). Transgender and gender nonbinary respondents will be grouped by gender identity (eg, transgender men and transmasculine persons with men).

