#### Intersectional Discrimination Index

All Spanish-language participants will receive the unattributed InDI (Multimedia Appendix 1), with potential modifications based on cognitive interview findings. For the English survey, we will use the block-randomization feature in Qualtrics to implement a split-ballot design: 1000 participants will receive each of the unattributed, item-level attributed, or overall attributed versions of the InDI.

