We will use mCFA to determine whether the configural, metric, and scalar structures of the InDI measures are equivalent across (1) language (English vs Spanish) and (2) the 12 intersectional race and ethnicity*SGM*gender sample strata. Achieving equivalence across all these scale structures is necessary for the InDI measures to generate meaningful cross-group comparisons. After estimating the baseline models for each group, we will test configural equivalence across language and intersectional strata. We will then assess the metric equivalence of the scales by examining whether factor loadings vary across these groups by comparing the fit of the metric models with those of the configural models. To assess scalar equivalence, item thresholds will be tested for their equivalence among the same groups. Formal comparisons will be carried out by comparing the fit of the scalar models with those of the metric models. To compare less (eg, configural) and more restrictive (eg, metric and scalar) models, we will use a reduction ≥0.002 in the value of the comparative fit index as an unbiased indication of lack of equivalence, given the sensitivity of *P* values to large sample sizes [75]. We will also assess the partial invariance of the InDI measures. If needed (eg, because of numerous large modification indices), the alignment method will be used as an alternative to assess measurement equivalence [76].

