##### Quantitative Analysis

As a first step, we will compare discrimination burden (mean or median score on each of the InDI-A, InDI-D, and InDI-M) across the three conditions for each measure (unattributed, item-level attribution, and overall attribution) to determine whether the presence of attributions influences reporting. We will use appropriate parametric and nonparametric statistics (eg, chi-square and Mann-Whitney U test) to test for statistically significant differences between conditions. Next, we will estimate concordance between intersectional SSPs and discrimination attributions to determine the extent to which attributions align with SSPs. Among those reporting any discrimination in both the item-level and overall attribution conditions, we will calculate the proportion of (1) Black or Latino/a/x individuals who report racial and/or ethnic discrimination, (2) SGM individuals who report sexuality and/or gender identity–related discrimination, and (3) Black or Latino/a/x SGM who report both types of discrimination. In the item-level attribution condition, we will further calculate the proportion of items for which the aforementioned groups endorsed the respective attributions.

Finally, we will compare the magnitude of effect on psychological distress (continuous) and fair or poor (vs good or excellent) self-rated general health of reporting each discrimination type (InDI-A, InDI-D, and InDI-M), (1) based on sexuality and/or gender identity, (2) based on race and/or ethnicity, or (3) based on both (1) and (2). Using data from the attributed conditions, we will fit linear regression models to separately estimate the association between a categorical indicator of discrimination attributions (race and/or ethnicity, sexuality and/or gender, both, or other attributions only) and psychological distress, adjusting for total discrimination burden. These analyses will be conducted separately among Black and Latino/a/x SGM reporting any discrimination for each measure (InDI-A, InDI-D, and InDI-M). Parallel analyses focused on attributions to race and/or ethnicity, gender, both, or other attributions will be conducted among Black and Latino/a/x women. For self-rated health, we will use a similar approach with logistic regression.

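### The English-vs-Spanish equivalence test confounds language with questionnaire version by design, and probably with ethnicity, so a failed test could not be attributed to language

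*Protocol article*

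**What the plan says.** **Contrast.** The Aim 2 analysis plan asks whether the configural, metric and scalar structures are "equivalent across (1) language (English vs Spanish"), and separately whether they are equivalent across 12 race and ethnicity by SGM by gender strata. A fall in CFI of 0.002 or more between nested models counts as lack of equivalence. For the language contrast, no questionnaire version or ethnic group is specified.

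**Version.** Under Quantitative Surveys, Intersectional Discrimination Index: "All Spanish-language participants will receive the unattributed InDI". In the English survey, "1000 participants will receive each of the unattributed, item-level attributed, or overall attributed versions of the InDI".

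**Ethnicity.** Participants sets English quotas of 1000 each for non-Hispanic Black, non-Hispanic White and Latino/a/x respondents. For the other survey it says only: "The Spanish survey (n=500) will include 250 SGM and 250 non-SGM". The Table 1 footnote attached to both surveys reads "Quota sampling by race and ethnicity and sexual or gender minority status", but no ethnic numbers are given for the Spanish sample.

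**Status of the version effect.** The Aim 3 Quantitative Analysis compares scores across the three versions "to determine whether the presence of attributions influences reporting".

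**The concern.** A multigroup CFA compares groups defined by one variable, as the Aim 2 text itself notes. If that variable is survey language, anything else that differs between the two samples is absorbed into it. Version differs by design. Ethnic mix very probably differs too.

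The protocol gives reasons not to treat either as harmless. The Introduction reports the argument that attributed and unattributed measures tap different constructs, and says this has not been tested. Aim 3 exists partly to find out. The Introduction and Discussion also cite evidence that existing discrimination scales function differently across US social groups. Aim 2 therefore relies on an answer that Aim 3 has yet to supply.

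Equivalence across language is part of the second primary aim, and bilingual validated measures are the key deliverable. A failed test could lead to revision of a sound Spanish version. A pass produced by offsetting effects could let a faulty one through. The Introduction motivates the question by response differences by survey language and acculturation among Latino/a/x people, which is narrower than the contrast as written.

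**Working it through.** **1. The plan's own figures.** 3 race and ethnicity groups × 2 SGM × 2 gender = 12 strata, and 12 × 250 = 3000. Three versions: 3000 / 3 = 1000 each. Both reproduce exactly. The 200-per-group minimum for 80% power comes from a cited simulation and cannot be re-derived from the article.

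**2. Overlap between the language groups.**

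| Feature | English (3000) | Spanish (500) |
|---|---|---|
| Unattributed version | 1000 (33.3%) | 500 (100%) |
| Attributed version | 2000 (66.7%) | 0 |
| Latino/a/x | 1000 (33.3%) | not stated |
| Non-Hispanic | 2000 (66.7%) | not stated |

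If versions split evenly within ethnicity, English respondents who are both Latino/a/x and on the unattributed version number 1000 / 3 ≈ 333, or 333 / 3000 ≈ 11%. The other 89% or so differ from a Latino/a/x Spanish respondent in version, ethnicity or both.

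**3. Can other planned analyses separate the causes?** The MIMIC covariates include race and ethnicity and nativity, but neither survey language nor version. Partial invariance and alignment can show which items differ, not why. The Aim 3 comparison by version is randomised but concerns total scores, not item thresholds. These tools mitigate the problem but do not resolve it.

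**4. Illustration of size.** All inputs in this step are assumptions except the group sizes (3000 and 500) and the 0.002 rule: one factor, 9 continuous items, no language effect, and intercepts shifted on a few items in a share of the English sample. At population level, CFI drop = (F_scalar − F_metric) / F_baseline, where F is the maximum-likelihood misfit.

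Loadings 0.7, 2 items shifted:

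| Share of English sample shifted | 0.2 SD | 0.3 SD | 0.4 SD |
|---|---|---|---|
| Two thirds | 0.0017 | 0.0039 | 0.0068 |
| One third | 0.0004 | 0.0010 | 0.0017 |

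With two thirds shifted, varying the loadings over 0.6 to 0.8 and the shifted items over 2 to 4 gives 0.0004–0.0009 at 0.1 SD, 0.0015–0.0034 at 0.2 SD and 0.0033–0.0075 at 0.3 SD.

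The drop depends almost entirely on share × shift: two thirds × 0.2 and one third × 0.4 both give 0.133 and a drop of 0.0017. So the one-third row is not safe at every size. At 0.5 SD it would be about 0.0017 × (0.5 / 0.4)² ≈ 0.0027.

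**5. Feasibility of a like-for-like contrast.** English Latino/a/x unattributed ≈ 333; Spanish Latino/a/x up to 500. The English group exceeds 200, and the Spanish group does so unless most of that sample is not Latino/a/x. Split by SGM status, the English group is 333 / 2 ≈ 167, below 200. Split also by gender, it is about 83.

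**The case against.** **The article is condensed.** It does not say that all 3000 English respondents enter the language test, and a fuller plan may restrict it. That is fair, but the version allocation and the contrast are both stated here, and run as written they produce the confounding. The sample-size section counts 250 per stratum across all 3000, whereas the unattributed version alone would give 250 / 3 ≈ 83. Pooling is therefore at least the working assumption for the 12-stratum test. For the language test, no English sample size is given.

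**The Spanish sample's ethnicity is inferred.** This stands. No passage gives it, and the Table 1 footnote implies some race and ethnicity quota. The version imbalance needs no inference and carries the point alone.

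**The versions are one instrument.** They appear to share core items and differ in the attribution requests; the appendix is not shown. A reader might infer that the two language groups answer different questionnaires, but the documents do not support that. If overall attributions are requested only after a measure's items, that third may answer much as the unattributed third does, and the version-affected share would be nearer one third.

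**The illustration rests on assumptions.** The documents give no size for a version or ethnic shift. The model applies one common shift to two thirds of the sample, although version and ethnicity cross. It uses continuous items, whereas the plan tests thresholds. A reader might infer that any version or ethnic effect will be reported as a failed Spanish version. It would not: the 0.2 SD case above, at 0.0017, is not flagged.

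**Restriction does not isolate language.** Spanish- and English-responding Latino/a/x people may still differ in nativity and acculturation. This also stands.

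**Conclusion.** The concern holds in a limited form. Language is confounded with questionnaire version by design and probably with ethnicity. As the contrast is written, a CFI drop of 0.002 or more could not be assigned to the Spanish version, and offsetting effects could mask a real language difference. This needs no assumption about size, because it follows from the allocation of versions and the unrestricted contrast.

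Whether the confounding would actually trip the rule is uncertain. Under the stated assumptions it is plausible for shifts of about 0.2 to 0.3 SD on a few items if two thirds of the English sample are affected. It is unlikely for shifts of that size if only one third is affected. The documents support neither a certain false failure nor a claim that the language test is uninformative; a clear pass would be less affected than a failure.

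**What to change.** Define the primary language mCFA as Latino/a/x English respondents randomised to the unattributed version against Latino/a/x Spanish respondents. Keep all-English vs Spanish as descriptive only. State the ethnic composition expected or required in the Spanish sample, and reconcile the Participants section with the Table 1 footnote.

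The cost is wording; no new data or change to the instrument is needed. The downsides to name are:

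- The English group falls from 3000 to about 333, assuming an even split of versions within ethnicity. This is still above the stated minimum of 200. Stratifying the version randomisation by ethnicity would secure the number.
- If the language comparison is further split by SGM status, the English group is about 167, below that minimum. Such a split should be labelled exploratory.
- Nativity and acculturation remain tied to survey language. The report should say so and should not attribute all remaining non-equivalence to translation.

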#### Aim 3: Determine Whether Attributions Should Be Included in the InDI Measures

##### Overview

Aim 3 will use a convergent mixed methods design; quantitative and qualitative data analyses will be conducted separately and then the findings will be integrated to identify areas of convergence and divergence [77], following the National Institutes of Health Best Practices guidelines for mixed methods research [78].

##### Qualitative Analysis

Transcripts will be uploaded to Dedoose cloud-based software for analysis, facilitating remote collaboration. We will code the portion of the interview in which participants reflect on attribution items as well as any other portions relevant to attribution (eg, if raised by a participant earlier in the interview). The analysis will use techniques adapted from grounded theory [79,80]. Inductive coding to identify emergent themes will follow the constant comparative method of going back and forth between the data and coding to identify patterns and regularities. Two analysts will read all transcripts. Each analyst will code 5 transcripts independently, at which point discrepancies will be resolved through discussion before the remaining transcripts are coded. We will compare codes and themes by age, race, ethnicity, nativity, urban or rural residence, gender, and sexual orientation. To establish credibility, we will maintain an audit trail of coding decisions.

##### Quantitative Analysis

As a first step, we will compare discrimination burden (mean or median score on each of the InDI-A, InDI-D, and InDI-M) across the three conditions for each measure (unattributed, item-level attribution, and overall attribution) to determine whether the presence of attributions influences reporting. We will use appropriate parametric and nonparametric statistics (eg, chi-square and Mann-Whitney U test) to test for statistically significant differences between conditions. Next, we will estimate concordance between intersectional SSPs and discrimination attributions to determine the extent to which attributions align with SSPs. Among those reporting any discrimination in both the item-level and overall attribution conditions, we will calculate the proportion of (1) Black or Latino/a/x individuals who report racial and/or ethnic discrimination, (2) SGM individuals who report sexuality and/or gender identity–related discrimination, and (3) Black or Latino/a/x SGM who report both types of discrimination. In the item-level attribution condition, we will further calculate the proportion of items for which the aforementioned groups endorsed the respective attributions.

Finally, we will compare the magnitude of effect on psychological distress (continuous) and fair or poor (vs good or excellent) self-rated general health of reporting each discrimination type (InDI-A, InDI-D, and InDI-M), (1) based on sexuality and/or gender identity, (2) based on race and/or ethnicity, or (3) based on both (1) and (2). Using data from the attributed conditions, we will fit linear regression models to separately estimate the association between a categorical indicator of discrimination attributions (race and/or ethnicity, sexuality and/or gender, both, or other attributions only) and psychological distress, adjusting for total discrimination burden. These analyses will be conducted separately among Black and Latino/a/x SGM reporting any discrimination for each measure (InDI-A, InDI-D, and InDI-M). Parallel analyses focused on attributions to race and/or ethnicity, gender, both, or other attributions will be conducted among Black and Latino/a/x women. For self-rated health, we will use a similar approach with logistic regression.

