## Discussion

### Study Importance

This study offers multiple innovations. It aligns with the National Institute on Minority Health and Health Disparities priorities for promoting the advancement of health disparities science by “strengthen[ing] the understanding of how racism and discrimination are conceptualized and measured, and how they contribute to health disparities” [84]. The key deliverables of this study will be bilingual measures of anticipated, day-to-day, and major discrimination validated for multiple health disparity populations using rigorous qualitative, quantitative, and mixed methods. Despite the high cognitive burden posed by discrimination measures, few studies have combined cognitive interviewing and psychometric approaches to validate them [85]. By subjecting these novel measures to a comprehensive and early evaluation of measurement equivalence, we will identify and be able to revise potentially problematic items before widespread use. Multiple studies have uncovered differential item functioning across diverse social groups among measures, such as the widely used Everyday Discrimination Scale [39,85,86], but only after they had been used in hundreds of studies [87] and were thus unlikely to be modified. The study will further advance measurement methods for health disparities research by determining the utility of including attributions in intersectional discrimination measures. If an attribution-free approach is viable, it will be possible to briefly assess discrimination experiences across a range of individual SSPs and their intersections in broad population surveys, enabling health disparities researchers to answer a much wider range of questions than with single-attribution measures.

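### Whether attributions influence reporting is judged only by tests for a difference, which cannot show that the three versions report alike; adjusted contrasts with confidence intervals and a preset smallest relevant difference would answer better from the same data

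*Protocol article*

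**What the plan says.** The section on the Intersectional Discrimination Index under Quantitative Surveys sets up a randomised comparison in the English survey: "we will use the block-randomization feature in Qualtrics to implement a split-ballot design", in which "1000 participants will receive each of the unattributed, item-level attributed, or overall attributed versions of the InDI".

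The Quantitative Analysis section of Aim 3 then compares discrimination burden across the three versions, using the "mean or median score on each of the InDI-A, InDI-D, and InDI-M". The stated purpose is "to determine whether the presence of attributions influences reporting". The criterion is given as a choice of suitable parametric and nonparametric statistics, with two examples: "eg, chi-square and Mann-Whitney U test) to test for statistically significant differences between conditions". That section states no smallest relevant difference and no interval estimate for the comparison between versions.

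Three other places bear on the point:
- Study Importance makes the wider use of the measures conditional: "If an attribution-free approach is viable".
- The Introduction reports that, in the preliminary study, people of color and sexual and gender minorities (SGM) reported more discrimination. Race and ethnicity and SGM status are two of the three factors that define the quota strata.
- The Sample Size section sizes the survey for multigroup factor analysis and gives no detectable difference for the comparison of versions.

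**The concern.** The question can be answered yes or no. A test for a difference can support yes, but its failure to reach significance does not support no: it may reflect similar reporting or limited precision. The no answer is the more useful one to someone deciding whether attribution items can be left out, or added, without changing the scores.

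The yes answer also needs a size. With 1000 per version, a small shift can be significant, and without a smallest relevant difference the reader cannot tell whether it matters for measurement.

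There are two lesser points of method. Mann-Whitney compares two groups, so three versions need either pairwise tests or a three-group test. And simple tests of this kind leave in the error term the variation between strata that a model could remove.

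**Working it through.** **Inputs.** From the documents: 1000 per version and three versions (Intersectional Discrimination Index, under Quantitative Surveys); 12 strata of 250 (Sample Size). Assumed, because the article does not give them: two-sided alpha of 0.05, scores in SD units with SD = 1, approximate normality, and margins of 0.10 to 0.20 SD.

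**The plan's own figure.** 12 × 250 = 3000 and 3 × 1000 = 3000, so the design totals agree.

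**What a difference test detects.**
- SE of a contrast = √(2/1000) = 0.0447 SD.
- Smallest observed difference that is significant = 1.96 × 0.0447 = 0.088 SD. This is also the half-width of the 95% CI.
- Difference detected with 80% power = (1.960 + 0.842) × 0.0447 = 0.125 SD (0.128 SD for Mann-Whitney under normality, relative efficiency 3/π).
- Power at true differences of 0.05, 0.10 and 0.15 SD: 20%, 61% and 92%.

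So a true difference of 0.10 SD is missed about 39% of the time (100 − 61). Non-significance is weak evidence of sameness at that size.

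**What the same data could say about similarity.** With two one-sided 5% tests and no true difference, power = 2Φ(m/0.0447 − 1.645) − 1 for margin m. If the 95% CI itself must lie inside the margin, 1.96 replaces 1.645.

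| Margin m (SD) | m/0.0447 | Power, two one-sided 5% tests | Power, 95% CI inside margin |
|---|---|---|---|
| 0.10 | 2.236 | 45% | 22% |
| 0.15 | 3.354 | 91% | 84% |
| 0.20 | 4.472 | 99.5% | 99% |

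For 80% power at 0.10 SD with the two one-sided tests, n per version = 2 × ((1.645 + 1.282)/0.10)² ≈ 1713, more than the 1000 planned.

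**Precision from adjusting for strata.** If the 12 strata explain a share R² of score variance, the SE is multiplied by √(1 − R²). The article gives no R². For assumed values of 0.05, 0.10 and 0.20, the 95% CI half-width falls from 0.088 to 0.085, 0.083 and 0.078 SD. The gain is real but modest.

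**Effects within strata.** 250/3 ≈ 83 per version per stratum. SE = √(2/83.3) = 0.155 SD, and the difference detected with 80% power is 2.802 × 0.155 ≈ 0.43 SD. Similarity within 0.20 SD could not be shown in a single stratum, because 1.645 × 0.155 = 0.255 exceeds the margin. Grouping helps: the four Black and Latino/a/x SGM strata hold 4 × 250 = 1000 people, about 333 per version, with a 95% CI half-width of 1.96 × √(2/333.3) = 0.152 SD.

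**The case against.** The defence has force on several points.

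- **The tests are examples.** The wording leaves analysis of variance or regression open, and Mann-Whitney is valid for pairwise contrasts. This stands: the article fixes no wrong test. What it does fix is the criterion, statistical significance.
- **The article never says that non-significance will be read as equivalence.** A reader might infer this from the stated purpose and from the hope for an attribution-free measure, but the text does not say it. The score comparison is an opening step. It is followed by concordance and health-association analyses and is then integrated with qualitative findings, so no rule lets this one test settle viability. This stands, and it limits the consequence.
- **Ignoring strata does not bias the contrast.** A reader might infer bias. Versions are randomised, so the loss is precision only.
- **Aim 2 does not contradict Aim 3.** A reader might set the remark in Aim 2 about the "sensitivity of *P* values to large sample sizes" against the use of significance here. That remark concerns the fit of nested factor models; it is an analogy, not an inconsistency.
- **Multiplicity.** The article is silent, and an analysis plan that is not shown may cover it. No fault follows from silence.
- **Trivial differences are not always flagged.** Power at 0.05 SD is only 20%, and whether 0.09 or 0.125 SD is trivial depends on a threshold the article does not give.
- **The Sample Size statement is not refuted.** It says the other planned analyses need fewer participants. The 1713 per version applies to an equivalence analysis with a tight margin, which the article does not plan.

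What remains is that the stated criterion can answer only half of the stated question.

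**Conclusion.** The concern holds in limited form. Significance testing is the only stated basis for judging whether attributions influence reporting. It cannot establish that the versions report alike, and it gives no guide to whether a significant difference of about 0.09 SD or more matters. Interval estimates from a stratum-adjusted model would be more informative and somewhat more precise, at the sample size already planned.

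On the assumptions above, 1000 per version can support a conclusion of similar reporting at margins of 0.15 SD or wider, but not at 0.10 SD. This holds under either interval rule in the table. The choice of margin therefore decides what the study can conclude, and it should be made before the data are seen. Skewed scores would change the exact figures.

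This is a should-fix improvement in method. It does not show that the planned comparison is biased or invalid.

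**What to change.** For each of the three measures, fit one model (linear, or ordinal or count for skewed scores) with version and the 12 quota strata as covariates. Use a three-group test such as Kruskal-Wallis as the rank-based check.

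Report the two contrasts of an attributed version with the unattributed version as standardised differences with 95% CIs. Fix a smallest relevant difference for each measure in advance, and say which interval is set against it: the 90% CI, which matches two one-sided 5% tests, or the stricter 95% CI. Conclude that reporting is similar only when that interval lies inside the margin, never from non-significance.

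Examine version-by-group effects in grouped strata, for example Black and Latino/a/x SGM respondents, and present them as descriptive. About 83 per version per stratum is too few for 12 separate conclusions.

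The cost is plan wording, slightly more analysis work, and the need for the investigators to choose and defend a margin. No extra data are required for a margin of 0.15 SD or wider; a margin of 0.10 SD would be underpowered at the planned size.

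### The Aim 3 concordance analysis counts matching attributions only among holders of the marginalised position, so a high value does not identify how far attributions align with position

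*Protocol article*

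**What the plan says.** In the protocol article, the Quantitative Analysis section under Aim 3 states the purpose of this step: "we will estimate concordance between intersectional SSPs and discrimination attributions to determine the extent to which attributions align with SSPs". The analysis set is given as "Among those reporting any discrimination in both the item-level and overall attribution conditions", and three proportions follow:

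- "1) Black or Latino/a/x individuals who report racial and/or ethnic discrimination"
- "2) SGM individuals who report sexuality and/or gender identity–related discrimination"
- "3) Black or Latino/a/x SGM who report both types of discrimination"

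For the item-level version the plan adds "the proportion of items for which the aforementioned groups endorsed the respective attributions", which keeps the same groups.

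The split ballot is described in the Intersectional Discrimination Index section under Quantitative Surveys: "1000 participants will receive each of the unattributed, item-level attributed, or overall attributed versions of the InDI". The Participants section sets quotas of 1000 Black, 1000 White and 1000 Latino/a/x respondents in English, with half of each group SGM.

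**The concern.** Concordance between two characteristics is a property of the whole cross-table: how often the attribution is made by people who hold the position, and how often by people who do not. The plan fills only the first row. If respondents of every group tended to tick race or ethnicity as a reason, the planned proportion among Black or Latino/a/x respondents would be high and would look like alignment.

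The article itself raises this possibility. Its section on asking for attribution warns that blurred boundaries between social positions may make the reasons respondents select arbitrary. The result also feeds the decision on whether the InDI should ask for attributions, where it matters whether attributions add to what cross-stratified demographics already show. A high proportion among holders could be read as evidence that they track position when the comparison that would show this was never made.

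**Working it through.** **1. Reproduce the plan's own figure.** No target or precision is stated for concordance. The figure behind the denominators is the English sample: 3 race and ethnicity groups × 2 SGM groups × 2 genders × 250 = 3000, as in the Sample Size section.

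**2. Numbers in the attributed conditions.** Two versions × 1000 = 2000. Expected composition, before restriction to those reporting any discrimination:

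| Group | Expected n |
|---|---|
| Black or Latino/a/x | 2000 × 2000/3000 = 1333 |
| White | 2000 × 1000/3000 = 667 |
| SGM | 2000 × 1500/3000 = 1000 |
| Non-SGM | 2000 × 1500/3000 = 1000 |

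The restriction lowers all of these by an amount the article does not give, so they are upper limits.

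**3. What is planned.** Let *s* be the share of holders making the matching attribution and *f* the share of non-holders making the same one, both among respondents reporting any discrimination. The planned quantities are all of type *s*; *f* is not planned. The other quantitative steps do not supply it. The first compares discrimination burden across versions, and the regressions are confined to Black and Latino/a/x SGM and to Black and Latino/a/x women.

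**4. What *s* alone allows.** The difference *s* − *f* must lie between *s* − 1 and *s*.

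- A low *s* caps it: *s* = 0.20 means at most 0.20.
- A high *s* leaves it wide open: *s* = 0.70 allows anything from −0.30 to 0.70.

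**5. Illustration.** All rates here are assumptions. With *s* = 0.70:

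| *f* | Planned result | *s* − *f* | Kappa, race axis | Kappa, SGM axis |
|---|---|---|---|---|
| 0.10 | 0.70 | 0.60 | 0.53 | 0.60 |
| 0.30 | 0.70 | 0.40 | 0.37 | 0.40 |
| 0.70 | 0.70 | 0 | 0 | 0 |

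Kappa = (observed agreement − chance agreement)/(1 − chance agreement). For the race axis at *f* = 0.10:

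- observed agreement = (1333 × 0.70 + 667 × 0.90)/2000 = 0.767
- chance agreement = 0.50
- kappa = 0.267/0.50 = 0.53

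Over *f* from 0.05 to 0.70, *s* − *f* runs from 0.45 to −0.20 when *s* = 0.50, and from 0.85 to 0.20 when *s* = 0.90.

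**6. Precision if the second row is added.** The 95% half-width is 1.96 × √[*s*(1 − *s*)/n₁ + *f*(1 − *f*)/n₀]. For *s* = 0.70, *f* = 0.10 on the race axis, with everyone reporting some discrimination: 1.96 × √(0.21/1333 + 0.09/667) = 0.034. Over *f* of 0.10, 0.30 and 0.70 and both axes, the half-width is 0.034 to 0.043 if all report discrimination and 0.047 to 0.060 if half do. These figures use both versions together. For one version alone, with half the numbers, multiply by √2 = 1.41: about 0.05 to 0.06, or 0.07 to 0.08 if half report.

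**The case against.** The strongest reply is that this is a descriptive step, and only one input to Aim 3 alongside the burden comparison, the regressions and the qualitative work. The article rests its attribution-free design mainly on a lack of evidence that health effects depend on attribution, and it nowhere says that attributions must be absent in people without the position. That is fair, and it limits the consequence. It does not close the gap between the stated purpose and the listed denominators. Nor is this a detail lost in condensing the article, because the groups are spelled out.

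Three stronger readings are tempting and are not supported:

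- **The planned figures say nothing about alignment.** They do speak in one direction, since a low value would show that many holders do not make the matching attribution.
- **The two attribution versions will be pooled, so that question format alone shifts the result.** The text refers to both conditions, which can equally mean each of them, and it then treats the item-level version separately. The questionnaire wording is in an appendix not shown, so no format effect can be demonstrated.
- **A White respondent citing race or ethnicity is in error.** Social position is not a gold standard for why someone was mistreated, so a diagnostic frame of sensitivity and specificity is not required. A plain comparison of proportions is enough.

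**Conclusion.** The point holds in a limited form. The purpose is concordance, but the listed quantities describe only position holders, and nothing else in the article supplies the White or non-SGM comparison. A high planned value therefore leaves the extent of alignment unidentified: at an assumed 70% among holders, the difference from non-holders could be 0.60 or 0 with the same reported result. The size rests on assumed rates; the structural conclusion does not. A reader might infer that 667 White and 1000 non-SGM respondents go unused, but these are ceilings before restriction to those reporting discrimination. The matter deserves correction because the remedy is nearly free. It does not undermine Aim 3 as a whole.

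**What to change.** Among those reporting any discrimination in the attributed conditions, compute the same proportions in the complementary groups:

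- White respondents for racial or ethnic attribution
- non-SGM respondents for sexuality or gender identity attribution
- the other race-by-SGM strata for the joint attribution

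Do the same for the per-item proportions in the item-level version. Report the holder minus non-holder difference with a 95% CI, separately by attribution version.

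If this is not done, describe the result as the share of position holders who make the matching attribution, and drop the word concordance and the claim about the extent of alignment.

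The cost is a few tables from data the survey already collects. No recruitment or questionnaire change is needed.
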